**Fig. 1 Fig1:**
[figure not shown]
Schedule of enrolment, interventions, and assessments

The control group infants will perform exclusively the individualized postural care program. They will perform the technique of respiratory facilitation and autogenous drainage modified only in the presence of clinically and radiographically established pulmonary atelectasis.

Both groups will follow the Individualized Family-Centered Developmental Care Program [17]. In particular, attention will be paid to the control of environmental stimuli such as soft lights during treatment to allow the baby to stay awake without being bothered by bright lights directly on the eyes and reduction of environmental noise (tone of the voice of the operators, noise of the monitors, cell phones).

All the interventions of the Individualized Family-Centered Developmental Care are in fact aimed at preventing and containing destabilization and neonatal discomfort considering the extreme sensitivity and vulnerability of these patients to environmental stimulation. In all newborns, the discomfort/pain measurement will be performed, using the Neonatal Pain, Agitation and Sedation Scale (NPASS) [18], according to our NICU protocol.

All patients will receive a loading dose of intravenous caffeine citrate (20 mg/kg) immediately after admission to the NICU, followed by a daily maintenance intravenous dose of 10 mg/kg. Demographic data on patient and maternal characteristics will be collected from each patient. In the two groups of infants, the following parameters will be continuously recorded and analyzed for the entire day, daily in the first week, and weekly after the first week of life: arterial oxygen saturation (SatO2) by Pulse Oximeter Masimo®; heart rate (HR); respiratory rate (RR): inspired fraction of oxygen (FiO2); episodes of apnea defined as cessation of breathing for more than 20 s, or a shorter respiratory pause associated with oxygen desaturation and/or bradycardia; episodes of bradycardia (HR< 80 bpm) or tachycardia (HR > 180 bpm); and secretions’ presence, NPASS Score, Silverman Anderson Score.

In the study group, infants will be also evaluated for vital parameters at T0, at the end of the reflex stimulations and 5 min after the end of the reflex stimulations, and evaluation of behavioral stability of children through the APIB scale (evaluation of preterm infant behavior) [19]. The APIB scale is based on behavioral articles defined according to the “Als Sinactive theory.”

The intervention in the study group will be continued also in case of intubation and start of MV during the entire hospital stay, to enhance respiratory function and favoring extubation.

Infants of both groups will receive 200 mg/kg of poractant alfa (Chiesi Farmaceutici, Parma, Italy) if they will need FiO_2_ ≥ 0.30 and CPAP of 6–7 cm H_2_O, by IN-SUR-E technique (if gestational age ≥ 28 weeks) or IN-REC-SUR-E technique [20] (if gestational age < 28 weeks), as per our NICU protocol. The indications for mechanical ventilation will be: poor oxygenation with FiO_2_ greater than 0.40 after rescue surfactant, respiratory acidosis (pCO_2_ > 65 mm Hg [8·5 kPa] and pH < 7·20), or apnea (more than four episodes of apnea per h or more than two episodes of apnea per h requiring ventilation with bag and mask), despite optimal nasal CPAP, nasal intermittent positive pressure ventilation, or bilevel positive airway pressure.

The analysis of our NICU data for the year 2017 showed how the incidence of intubation and mechanical ventilation in the first week of life in preterm infants with GA ≤ 30 weeks, not intubated in the delivery room stands at 50%. The expected effect of the intervention proposed in the trial is an absolute risk reduction of 25% (relative risk reduction of 50%) from the expected control group rate.

Considering an α error of 0.05 (two-tailed) and a study power of 80%, 66 newborns are expected to be enrolled per arm (132 total newborns); this number will be increased by 10% to take account of any dropouts.

Statistical analysis will be carried out using the “intention to treat” method; all data will be collected in a single database and analyzed to evaluate any differences between the randomized groups both for primary outcomes and for secondary outcomes. Any associations between individual dependent and independent variables will be evaluated initially and the choice of statistical methods will be decided according to the nature of the variables (categorical, continuous, rank-order) and their distribution (normal, non-normal, other). Statistical analyses will be performed using the “Stata Statistical Software: Release 15.1 software (StataCorp LP, College Station, TX).”

Infants will be randomly allocated in a 1:1 ratio to receive either technique of respiratory facilitation (intervention group) or individualized postural care (control group). Ralloc, a Stata/IC 15.1 for Windows (Stata-Corp, College Station, TX), will be used to provide a sequence of treatments randomly permuted in blocks of varying size and order. Allocation concealment will be ensured by sequentially numbered, opaque, sealed envelopes.

The study protocol was approved by the Ethics Committee of the Fondazione Policlinico Universitario A. Gemelli IRCCS, Rome, Italy, with the approval number 9108/18 ID: 1906. Written and oral information will, whenever possible, be offered to parents if their infant is likely to be eligible. Informed written consent will be signed from both the parents and sufficient time will be provided for consent.

We used the SPIRIT reporting guidelines [21].

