## Methods

The primary hypothesis of this study is a reduction in the need of mechanical ventilation (MV) in the first week of life (excluding the transient tracheal intubation performed for surfactant administration) in spontaneously breathing infants born at 24^+0^–30^+6^ weeks’ gestation receiving a respiratory facilitation maneuver according to the reflex stimulations compared to exclusive standard individualized postural care program.

The secondary outcome will be:

(i) Duration of mechanical ventilation (MV) during the hospital stay;

(ii) Duration of O_2_-therapy during the hospital stay;

(iii) Bronchopulmonary dysplasia (BPD): O_2_-dependence at 36 weeks of postmenstrual age;

(iv) Duration of non-invasive ventilation (NIV) during the hospital stay;

(v) Post-conceptional age attainment of complete respiratory autonomy (absence of any kind of respiratory support and oxygen);

(vi) Pulmonary atelectasis diagnosed on chest X-ray and/or lung ultrasound;

(vii) Length of hospital stay;

(viii) Survival.

Additional data recorded for each infant will include occurrence of: pneumothorax; pulmonary interstitial emphysema; pulmonary hemorrhage; hemodynamically significant patent ductus arteriosus requiring treatment with ibuprofen; grade 3–4 intraventricular hemorrhage [6]; periventricular leukomalacia worse than grade 2 [7]; retinopathy of prematurity [8]; necrotizing enterocolitis [9]; sepsis, defined as a positive blood culture or suggestive clinical and laboratory findings leading to treatment with antibiotics for at least 7 days despite absence of a positive blood culture; and use of systemic postnatal steroids.

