This will be an unblinded mono-center randomized trial conducted at Fondazione Policlinico Universitario A. Gemelli IRCCS’s NICU. Eligible candidates will be preterm newborns with gestational age (GA) < 31 weeks not intubated in the delivery room and requiring non-invasive respiratory support. Exclusion criteria will be as follows: outborn, presence of major congenital malformations and/or genetic syndromes, fetal hydrops, inherited disorders of metabolism, persistent pulmonary hypertension of the newborn, severe circulatory shock (prolonged capillary filling, reduced strength of peripheral pulses, cool skin, lethargy, hypotension, oliguria, increasing lactate concentrations and metabolic acidosis), and other unstable clinical conditions at the time of randomization for which the newborn cannot perform the physiotherapy treatment required by the study.

All preterm infants managed in our NICU routinely follow routinely the program of individualized postural care [10–15], which include handling and positioning of the infant. Neonatal nurses and physiotherapists can play a major role in designing, modeling, and teaching positioning strategies that promote oxygen saturation stability, skeletal integrity, postural control, and sensorimotor organization. The individualized postural care program consists in alternating postures according to the needs of each individual infant. The postures are alternated in 24 h and are prone, supine, and lateral with adequate postural supports.

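### The pCO2 limit in the respiratory-acidosis indication for mechanical ventilation is printed as two values that are not equal: 65 mm Hg is 8.67 kPa, not 8.5 kPa

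*Protocol article*

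**What the plan says.** All references are to the protocol article, Methods.

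- **Primary outcome.** The primary hypothesis is "a reduction in the need of mechanical ventilation (MV) in the first week of life". Brief intubation for giving surfactant does not count.
- **Indications for ventilation.** Three alternatives are listed: "poor oxygenation with FiO_2_ greater than 0.40 after rescue surfactant"; "respiratory acidosis (pCO_2_ > 65 mm Hg [8·5 kPa] and pH < 7·20"; and "apnea (more than four episodes of apnea per h or more than two episodes of apnea per h requiring ventilation with bag and mask". The list closes by requiring that non-invasive support has already been optimised.
- **The figure at issue.** In the second alternative the pCO2 limit appears in mm Hg, with a kPa value in square brackets as its equivalent. This is the only kPa figure in the article, and nothing elsewhere repeats or explains it.
- **Setting.** The design statement reads "This will be an unblinded mono-center randomized trial". The indications are stated once, with no separate version for either arm.

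**The concern.** A bracketed second unit tells the reader that both numbers are the same limit. Here they are not, so the criterion can be read in two ways. An infant whose pCO2 lies between the two values, with pH below 7.20, meets it if 8.5 kPa is applied and does not if 65 mm Hg is applied.

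The slip deserves a correction because of where it stands. The three indications are the only criteria that the article gives for starting mechanical ventilation, and starting it in the first week is the primary event. The staff who apply them are not blinded to allocation. A criterion with that role should have one reading.

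**Working it through.** **Inputs**

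- Limit in mm Hg: 65 (Methods, indications for mechanical ventilation).
- Limit in kPa: 8.5 (same sentence).
- Conversion: 1 mm Hg = 0.133322 kPa. This is a fixed relation between units. It is not stated in the article.

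**Step 1: try to reproduce the plan's kPa figure.**
65 × 0.133322 = 8.666 kPa, which is 8.67 to two decimals and 8.7 to one. The printed 8.5 is not reproduced.

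**Step 2: convert the other way.**
8.5 / 0.133322 = 63.76 mm Hg, or 63.8 to one decimal.

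**Step 3: size of the gap.**

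- In mm Hg: 65 − 63.76 = 1.24.
- In kPa: 8.67 − 8.50 = 0.17.
- Relative: 1.24 / 65 = 1.9%.

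**Step 4: could rounding explain it?**

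| Printed value | Range that rounds to it | Same range in the other unit | Contains the other printed value? |
|---|---|---|---|
| 8.5 kPa | 8.45 to 8.55 kPa | 63.4 to 64.1 mm Hg | No (65) |
| 65 mm Hg | 64.5 to 65.5 mm Hg | 8.60 to 8.73 kPa | No (8.5) |

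Cutting 8.666 off at one decimal gives 8.6, which does not match either. Only rounding to the nearest half kPa gives 8.5, and the text does not indicate such a convention.

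**Step 5: which infants are affected?**
The two readings differ only if all of these hold at the time of the decision:

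1. pCO2 is between 63.8 and 65 mm Hg.
2. pH is below 7.20.
3. The oxygenation indication is not met.
4. The apnea indication is not met.

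For the primary outcome to change, the infant must also not become ventilated for any reason later in the first week. The article gives no distribution of pCO2, so the number of such infants cannot be calculated.

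**Step 6: does the sample size depend on the limit?**
Its inputs are a control rate of 50% ("not intubated in the delivery room stands at 50"), the target effect ("absolute risk reduction of 25% (relative risk reduction of 50"), and "Considering an α error of 0.05 (two-tailed) and a study power of 80%, 66 newborns are expected to be enrolled per arm". With p1 = 0.50, p2 = 0.25, mean 0.375 and difference 0.25:

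- Without continuity correction: n = [1.960 × √(2 × 0.375 × 0.625) + 0.842 × √(0.25 + 0.1875)]² / 0.25² = 57.7, so 58 per arm.
- With continuity correction: (57.7 / 4) × [1 + √(1 + 4 / (57.7 × 0.25))]² = 65.4, so 66 per arm.

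The planned 66 is reproduced with the continuity correction. The pCO2 limit does not enter the calculation.

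**The case against.** The strongest reply is that the working limit is readable. The comparison sign is attached to the mm Hg value, which comes first. The kPa value is a bracketed conversion, and nothing shows that this single centre works in two units. On that view the sentence contains one threshold and one imprecise conversion. This stands as a reason to expect little harm. It does not make the two numbers equal, and the article contains nothing else that settles the matter.

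It is also true that pCO2 alone triggers nothing. It counts only together with pH, after optimised non-invasive support, and as one of three routes. That stands in full and limits the reach of the point.

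A reader might go further and infer that the primary endpoint itself is ambiguous, so that events would be counted differently in each unit. The article does not support this. The outcome is mechanical ventilation in the first week, and no procedure is described for classifying events by blood gas. A ventilated infant is an event in either unit. The discrepancy can act only through the bedside decision to start ventilation.

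A reader might also infer that one reclassified infant could tip the result or bias the comparison. One event can do that only when a result already lies at the significance boundary, and then so can any event, whatever its cause. No limit specific to an arm is stated, and equal shifts in equal-sized arms leave the risk difference unchanged. Lack of blinding is a separate matter, to which a gap of 1.9% adds little.

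**Conclusion.** The figure is wrong as printed. The two pCO2 values in the respiratory-acidosis indication differ by 1.24 mm Hg (0.17 kPa, about 1.9%), and no ordinary rounding reconciles them. It is worth correcting because the criterion governs when infants may be ventilated and ventilation is the primary event. The severity is the lowest.

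The effect on the trial is probably very small. That judgement rests on the narrow band, the additional conditions that must hold together, and a limit stated once for both arms. It remains a judgement, because the article gives no pCO2 data from which to count affected infants. The arithmetic needs no assumption beyond the unit conversion. The point does not touch the sample size, and it does not show bias or an undefined primary outcome.

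**What to change.** The sponsor should reconcile the two pCO2 figures in the indications for mechanical ventilation so that they express one threshold. The value intended is for the sponsor to confirm; this review does not say which is right and proposes none.

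The cost is one corrected figure in the protocol. If the same pair of values is repeated in site instructions or case report form guidance, which were not available here, those need the same correction. No change to the design, sample size or analysis follows.

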## Safety

Safety end-point measures will include incidence, severity, and causality of reported serious adverse events (SAE), namely changes in occurrence of the expected common prematurity complications and clinical laboratory test assessments, and the development of unexpected SAEs in this high risk population. All SAEs will be followed until satisfactory resolution or until the investigator responsible for the care of the participant deems the event to be chronic or the patient to be stable. All expected and unexpected SAEs, whether or not they are attributable to the study intervention, will be reviewed by the principal investigator and by all the authors to determine if there is reasonable suspected causal relationship to the intervention. If the relationship is reasonable, SAEs will be reported to the Ethics Committee to guaranty the safety of participants.

## Discussion

The technique of respiratory facilitation is based on the reflex stimulations, applied early to the preterm infant. The slight digital pressure is exerted on a hemithorax on a so called “trigger point.” Stimulating the trigger point will stimulate the respiratory activity by determining a compression on the stimulation side with consequent increase of the ipsilateral pulmonary ventilation/minute and the facilitation of the contralateral pulmonary expansion. This mechanism will determine the concatenation of input to all anatomical structures in direct and indirect relation to the area being treated, on the basis of the mechanical-neurological-fluidic links of the human body. The above-mentioned maneuver will determine three different consequences at a distance that will positively influence the respiratory dynamics of the preterm infant. According to Sherrington’s law, in fact, a muscle subjected to a stretch will respond with a contraction of its fibers in proportion to the stretching itself. Therefore, the ipsilateral compression will cause a stretch of the muscle fibers of the diaphragm and intercostal muscles which will activate its subsequent muscular contraction and a variation of the pulmonary volume from the stimulus side with consequent increase of the pulmonary ventilation, and concurrently, there will be a greater expansion of the contralateral hematitis. From the neurological point of view, the action of the diaphragm on the phrenic nerve, on the vagus nerve, and on the orthosympathetic level should be considered. Stimulation of the VII-VIII coast will bring three different neurological information. The first at the level of D7-D8-D9 with associated neurovegetative stimulation of this area that performs its viscosymal function at the visceral level. The second concerns the vagus nerve (X n.c.) which passes through the esophagus in the esophageal hiatus and is affected by structural modifications of the diaphragm. The third in the phrenic level as a modification of the muscular mobility will determine a modification of the action of the nerve that innervates it. From a fluidic point of view, the diaphragmatic stimulation with consequent improvement of the respiratory dynamics and of the same diaphragm muscle will lead to an improvement of the caval system, since the vena cava passing through the diaphragm can better guarantee a venous return with a consequent improvement also of the portal system.

## Trial status

The trial has been registered at UMIN- CTR trial (Identifier: UMIN000036066) on March 1, 2019 protocol no. 1and it is currently recruiting study subjects. It was started on March 17, 2019. It will be completed on, approximately, May 2021.

## Data Availability

After publication of the trial report, formal request for study data should be made to the corresponding author (GV) using a data request form delineating research aims, methods, and the variables needed. Such requests will be considered by the coordinator (GV) and core team (MT, FC). If research questions and methods are considered relevant and valid, the data management department of the Policlinico Universitario A. Gemelli IRCCS will securely transfer the requested, fully anonymized data in the desired format to the party under data transfer agreement. The team will decide about co-authorships, after discussion with the interested party about this. Data requests can be submitted at any time and the data will be accessible for 12 months from publication, with possible extension considered.

## Abbreviations

NICU: Neonatal intensive care unit
MV: Mechanical ventilation
RDS: Respiratory distress syndrome
CPAP: Continuous positive airway pressure
FRC: Functional residual capacity
BPD: Bronchopulmonary dysplasia
NIV: Non-invasive ventilation
SatO_2_: Arterial oxygen saturation
HR: Heart rate
RR: Respiratory rate
FiO_2_: Inspired fraction of oxygen
NPASS: Neonatal Pain, Agitation and Sedation Scale
